### Data collection

Data on prescription errors was captured in two formats. One set of data consisted of data points recorded on a form during callbacks to the participating physicians' offices from pharmacies regarding prescription errors. A second set of data was derived from forms completed by the hospital internal pharmacy for each prescription filled there. These forms also include indicators related to prescribing errors and legibility. Data forms were collected weekly and transcribed into a database for analysis.

To guarantee privacy and confidentiality, all research data were kept within the hospital by professional staff operating under codes of conduct and using encrypted data capture systems. All patient and prescription data were anonymized after linkage. The electronic prescribing technology uses the highest existing levels of data encryption and its mode of operation conforms to professional obligations on confidentiality and Canadian and Ontario privacy laws.

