### Outcomes

The principle outcome measure was total prescribing error, as measured by the number of call backs received from pharmacists to prescribing physicians offices. These are defined as potential medication errors picked up by the pharmacist at the time the prescription is filled. Rates will be compared between intervention and control weeks. Prescribing errors can take many forms and are of different levels of severity and a single prescription can have several errors and all will be counted. The denominator for total error is the total number of prescriptions and the numerator is the sum of the following types of error:

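### The primary outcome counts call-backs logged at offices of prescribers who know the allocation, so a 20% relative difference in capture would equal the whole target effect; the internal-pharmacy forms need a stated role as a check

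*Protocol article*

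**What the plan says.** The Outcomes section of the protocol article makes the primary outcome "total prescribing error, as measured by the number of call backs received from pharmacists to prescribing physicians offices". It describes what is counted as "potential medication errors picked up by the pharmacist at the time the prescription is filled", and adds: "The denominator for total error is the total number of prescriptions".

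The Data collection section states: "Data on prescription errors was captured in two formats". The first set is "data points recorded on a form during callbacks to the participating physicians' offices from pharmacies regarding prescription errors". The second comes from "forms completed by the hospital internal pharmacy for each prescription filled there", and these forms also carry indicators of prescribing error and legibility. The section does not say whether the second set feeds the primary numerator, replaces call-backs for those prescriptions, or serves as a check. It does say: "All patient and prescription data were anonymized after linkage".

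Under Study design, on weeks use the PDA and off weeks use paper, with allocation concealed only until the week begins. Sample size and analysis plan sets the target as an absolute fall of 5% from a control error rate of 25%.

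**The concern.** Every prescription is in the denominator, but under the Outcomes wording a detected error reaches the numerator only through a call-back. An error that the pharmacist notices and settles without phoning, or phones about without a form being completed, is scored as a correct prescription. Capture is partly discretionary. The interactions component includes trivial and extremely rare interactions, which a pharmacist might not phone about, and the legibility component is the pharmacist's opinion.

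Prescribers know whether the system is on, and pharmacists can probably tell a printed or faxed prescription from a handwritten one. If phoning or logging differs between on and off weeks, the difference looks exactly like a treatment effect. Randomising weeks does not remove it, because it arises after allocation, and more weeks do not reduce it. At stake is whether the result can be read as a change in prescribing error, or only as a change in recorded call-backs.

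**Working it through.** **Inputs from the article:** control rate 25%; target 25% − 5% = 20%; two-sided test at 5%, 80% power (Sample size and analysis plan). **Assumed, because the article gives no figure:** the capture fractions, and the share *s* of prescriptions filled at the internal pharmacy.

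**1. The target as a ratio.** 20/25 = 0.80. The usual two-proportion formula for 25% against 20%, with equal allocation, gives
(1.960 × √(2 × 0.225 × 0.775) + 0.842 × √(0.25 × 0.75 + 0.20 × 0.80))² / 0.05² ≈ 1,094 effective prescriptions per arm.
The stated 65 weeks do not follow from this if the week is the cluster with ICC 0.05: the minimum is 0.05 × 2 × 1,094 = 109.4 weeks, however many prescriptions each week yields. Prescriptions per week are not stated, so the basis of the 65 weeks cannot be recovered. Nothing below depends on it.

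**2. Model.** In each arm, observed rate = rate of pharmacist-detected errors × fraction of those phoned in and logged. Hence observed ratio = true ratio × capture ratio.

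**3. No true effect (true ratio 1).** An on/off capture ratio of 0.80 gives 25% × 0.80 = 20%, the whole target. A ratio of 0.90 gives 22.5%, half of it. If phoning and logging each fall by about 10.6%, the product is 0.894 × 0.894 = 0.80.

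**4. The same ratio in percentage points of capture:**

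| Off-week capture | On-week capture giving ratio 0.80 | Gap |
|---|---|---|
| 100% | 80% | 20 points |
| 80% | 64% | 16 points |
| 50% | 40% | 10 points |

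**5. Opposite direction.** With a true fall from 25% to 20%, a capture ratio of 1.25 gives 20% × 1.25 = 25%, so the effect disappears.

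**6. Chance of a false significant benefit** with no true effect, at 1,094 effective prescriptions per arm:

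| Capture ratio | Apparent on-week rate | Chance |
|---|---|---|
| 0.95 | 23.75% | 10% |
| 0.90 | 22.5% | 28% |
| 0.85 | 21.25% | 55% |
| 0.80 | 20% | 80% |

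Without a capture difference the figure would be 2.5%.

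**7. If the internal-pharmacy forms do enter the numerator,** with equal capture in both arms for that share *s*, the ratio *r* needed among the other prescriptions solves s + (1 − s)r = 0.80, so r = (0.80 − s)/(1 − s). For s = 20%, r = 0.60/0.80 = 0.75. For s = 50%, r = 0.30/0.50 = 0.60. A larger capture difference is then needed, but the forms are no longer an independent check.

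**The case against.** The strongest reply is that Data collection presents both sets of forms as error data. A reader might infer from Outcomes alone that an error counts only if it is phoned in and logged at an office. The text does not settle that, because the internal-pharmacy forms may also feed the numerator. This stands, and it is why the two sections need reconciling.

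A reader might also infer that everyone who handles the data knows the allocation. That is certain for prescribers and likely for pharmacists, but the article does not say who completes the call-back form. Errors are found at filling, which need not fall in the week of prescribing, so the office's status at the time of the call need not be the prescription's arm. This stands too.

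The outcome is defined by what the pharmacist picks up, so a missed error lies outside it rather than being misrecorded. The internal-pharmacy forms cannot reveal missed errors either. They test phoning and logging, in one pharmacy whose share is not stated.

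The same physicians supply both arms, so stable differences between offices largely balance. That is right, but it does not help if capture changes between on and off weeks within an office.

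Finally, this is a condensed article, and a check on capture may be in the full protocol or analysis plan; what was linked before anonymisation is not stated. The absence of a described check is therefore not the fault raised here. The outcome definition, and the open role of the second data source, are in the article itself.

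**Conclusion.** The narrower point holds. The primary outcome depends on call-back capture in an open comparison. A capture ratio of 0.80 would reproduce the full 25% to 20% target with no true effect, and a ratio of 1.25 would hide it. This assumes that capture acts multiplicatively and that call-backs alone form the numerator; if the internal forms count as well, the ratio needed elsewhere is more extreme (0.75 at an assumed 20% internal share).

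The documents do not support saying that capture did differ, that any bias favours the software, or that the difference required is small. It is 20 percentage points at full off-week capture and 10 points at 50%. Nor would every fall in call-backs be an artefact: fewer legibility calls because prescriptions are printed would be a real effect. The change is worth making because an arm comparison that does not depend on phoning or logging needs no new data.

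**What to change.** 1. Reconcile Outcomes with Data collection: state whether the internal-pharmacy forms enter the primary numerator. The preferred choice is to keep them separate from the call-back count, so that they remain an independent check.
2. Pre-specify a sensitivity analysis comparing the error rate on those forms between on and off weeks, with prescriptions classified by the week of prescribing. This needs no link to the call-back forms, provided the prescribing week can be recovered.
3. Where records can still be linked, also report by arm the fraction of form-flagged errors that have a matching call-back form.
4. Do not make the main claim conditional on dividing the overall call-back rate by this fraction. It comes from one in-house pharmacy, whose phoning habits may differ from those of outside pharmacies.
5. If the check disagrees with the primary result or cannot be done, word that result as a difference in recorded call-backs.

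Cost: analysis-plan wording, one extra comparison on data already collected and, where feasible, one record match. The article reports the trial as already conducted and the data as anonymised after linkage, so the match may no longer be possible. The check is less precise than the main analysis, covers an unstated share of prescriptions, and cannot exclude biased detection by pharmacists who see the prescription's format.

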## Discussion

This trial will be able to evaluate electronic prescribing in a hospital setting effectively while preserving the benefits of randomization to reduce bias. Its design takes into account the need for internal and external validity, that the results are attributable to the intervention and that they may be applied to general practice. This design is practical and does not interfere with usual physician workflow.

The findings from this trial will provide important information about the role of electronic prescribing in the ambulatory setting for clinicians and healthcare policy-makers in distinguishing.

One of the key decisions that required consideration in the design of this trial was the question of the appropriateness of physician- or cluster-level randomization. Rather than allocating physicians between the two groups using a random process, cluster-level randomized trials allocate groups of participants. In this study we randomized by time periods. The rationale for this randomization scheme is apparent when there is a high risk of heterogeneity between groups and to allow for the participating physicians to serve as their own controls groups.

This study will be the first published randomized control trial designed to evaluate the effectiveness of electronic prescribing in reducing prescription error in an ambulatory setting. Although technology applications related to patient safety and human error reduction are sweeping the healthcare landscape, it is important that we do not fall in to the same trap as our forefathers did with medications and snake oils. It is as important if not imperative to rigorously evaluate these applications in pragmatic, real-world fashion so that we can determine if they are truly effective or more of a hindrance than help. We look forward to adding the results of this trial to the growing body of literature in this area.

## Abbreviations

ADE – Adverse drug event

CPOE – Computerized physician order entry

PDA – Personal digital assistant
